## Abstract

**Introduction:**

Clinical depression is usually treated in primary care with psychological therapies and antidepressant medication. However, when patients do not respond to at least two or more antidepressants within a depressive episode, they are considered to have treatment resistant depression (TRD). Previous small randomised controlled trials suggested that pramipexole, a dopamine D2/3 receptor agonist, may be effective for treating patients with unipolar and bipolar depression as it is known to influence motivational drive and reward processing. PAX-D will compare the effects of pramipexole vs placebo when added to current antidepressant medication for people with TRD. Additionally, PAX-D will investigate the mechanistic effect of pramipexole on reward sensitivity using a probabilistic decision-making task.

**Methods and analysis:**

PAX-D will assess effectiveness in the short- term (during the first 12 weeks) and in the longer-term (48 weeks) in patients with TRD from the UK. The primary outcome will be change in self-reported depressive symptoms from baseline to week 12 post-randomisation measured using the Quick Inventory of Depressive Symptomatology Self-Report (QIDS-SR16). Performance on the decision-making task will be measured at week 0, week 2 and week 12. Secondary outcomes include anhedonia, anxiety and health economic measures including quality of life, capability, well-being and costs. PAX-D will also assess the adverse effects of pramipexole including impulse control difficulties.

**Discussion:**

Pramipexole is a promising augmentation agent for TRD and may be a useful addition to existing treatment regimes. PAX-D will assess its effectiveness and test for a potential mechanism of action in patients with TRD.

**Trial registration number:**

ISRCTN84666271

## Introduction

When patients do not respond to at least two or more antidepressants within a depressive episode, they are considered to have treatment resistant depression (TRD). This accounts for roughly 20%–30% of all depressed patients and is a leading cause of morbidity and workdays lost. Currently there is a shortage of effective pharmacological options for patients who fall within this category.^1^

The large, pragmatic Sequenced Treatment Alternatives to Relieve Depression (STAR*D) trial suggested that the chances of remission with conventional pharmacological approaches for patients with TRD are less than 15%.^2^ A systematic review^3^ indicated that the best, current, evidence-based treatment is addition of atypical antipsychotic medications such as aripiprazole or quetiapine. However, these agents are only moderately effective and have high dropout rates associated with adverse effects. The extent and frequency of these adverse effects (sedation, weight gain and movement disorders) mean that this ‘atypical augmentation’ is widely disliked by patients. Another option is adding lithium to an antidepressant, but the evidence base is limited and lithium is poorly tolerated, potentially toxic and again disliked by patients. No new antidepressant is more effective than tricyclic antidepressants which were discovered serendipitously over 60 years ago. The pharmaceutical industry has largely withdrawn from this area because of the difficulty of making real advances.

There is preliminary evidence that the dopamine agonist, pramipexole, could represent an important advance in TRD. A systematic review by Tundo *et al*
4 identified five completed randomised controlled trials (RCTs), three open-label trials and five observational studies of pramipexole for patients with major depressive episodes and reported beneficial effects of pramipexole for patients with unipolar and bipolar depression. An RCT by Cusin *et al*
5 with 65 unipolar TRD patients found significant benefit of pramipexole, administered at a relatively low average dose of 1.3 mg/day, over placebo on a continuous outcome symptom measure but not in terms of response (40% vs 27%). Another RCT by Corrigan *et al*
6 examining pramipexole monotherapy in non-treatment resistant unipolar depression found that 1 mg was superior to placebo, while 0.375 mg was ineffective and 5 mg caused very high drop out. A very small study by Franco-Chaves *et al*
7 (n=13 per group) of unipolar patients resistant to a single previous antidepressant randomised to receive pramipexole monotherapy (target dose=2.25 mg), pramipexole combined with escitalopram or escitalopram monotherapy, found no statistical difference between the study groups, although only four patients in the combined group completed the study. Two RCTs of bipolar depression by Zarate *et al*
8 and Goldberg *et al*
9 found that patients on pramipexole (average dose of 1.7 mg) were more likely to have better therapeutic response than those on placebo. A case series of TRD patients treated in the US by Fawcett *et al*
10 reported very good therapeutic responses to pramipexole augmentation of antidepressant therapy in 42 patients with depression at a mean dose of around 2.5 mg/day. However, given the small sample sizes and inconsistent results summarised above, the review by Tundo *et al*
4 concluded that adequately powered RCTs of pramipexole for depression are still needed.

The target dose of pramipexole used in PAX-D will be 2.5 mg/day as a single dose. The target dose was selected to be above the average achieved dose of the Cusin *et al* study^5^ and between the effective 1 mg/day dose and non-tolerated 5 mg/day dose of the Corrigan *et al* study,^6^ while keeping within the smPC upper limit of 4.5 mg/day. The dosing schedule, with medication administered once daily rather than in divided doses as in Cusin *et al*,^5^ followed that reported for participants under 45 years of age in the Fawcett *et al* case series.^10^

Pramipexole is of particular interest because it is a selective dopamine D2/D3 receptor agonist and therefore pharmacologically distinct from currently available antidepressants which mostly act to increase levels of serotonin in the synapse. Experiences of low motivation and anhedonia are thought to be related to the function of the central dopaminergic system which is not specifically targeted by current medicines.^11^ Dopaminergic signalling is believed to be required when learning about rewarding outcomes.^12^ Previous studies of pramipexole in patients with Parkinson’s disease^13^ and bipolar disorder^14^ completing reward learning tasks indicated that it acted to increase reward sensitivity (ie, to cause patients to treat rewarding outcomes as if they were more valuable). This raises the possibility that increased reward sensitivity is a cognitive mechanism by which pramipexole improves symptoms of depression. Pramipexole is also studied in an ongoing trial about TRD in bipolar disorder.^15^

### Objectives

The primary objective of PAX-D is to assess the efficacy of adding pramipexole to conventional antidepressant medication for treating symptoms of depression. Pramipexole will be administered under double-blind, placebo- controlled conditions in patients with TRD. Second, PAX-D will examine the effect of pramipexole on reward sensitivity and whether this may predict treatment outcome. A decision-making task^16^ will be used in the current trial to measure the impact of pramipexole on reward sensitivity. The relationship between pramipexole treatment, change in reward sensitivity and symptomatic response will be formally assessed using a mediation analysis. Further, the trial will estimate the degree to which baseline and initial changes in reward sensitivity are able to predict response to pramipexole, providing a first test of the potential for these measures to be deployed in the selection of treatments for TRD patients. Finally, PAX-D will conduct an economic analysis of pramipexole and its longer-term effect on quality of life, capability, well-being, functioning and costs. Finally, the acceptability and tolerability of pramipexole will be assessed across the course of treatment. All objectives are summarised in table 1.

**Table 1 T1:** Study objectives (from https://www.isrctn.com/ISRCTN84666271)

Objectives	Outcome measures	Time points
Primary objective	Primary outcome	
To compare the efficacy of pramipexole and placebo at 12 weeks postrandomisation	Improvement (change from baseline) of depressive symptoms measured on the QIDS-SR_16_	Week 1–12
Secondary objectives	Secondary outcomes	
To compare the tolerability and safety of pramipexole and placebo during the 48-week treatment phase	Tolerability assessed by: Termination of trial treatment due to intolerance Adverse reactions TSQM-9 Safety–emergence of new symptoms: ALTMAN (manic symptoms) QUIP-RS (impulse control) Suicidal ideation (QIDS-SR_16_)	Weeks 1–48
To compare the effect of pramipexole and placebo on reward sensitivity	Change in reward sensitivity parameter from model fitted to learning/decision making task between baseline, week 2 and week 12	Baseline, week 2, week 12
To test the degree to which change in reward sensitivity mediates the 12 weeks response to pramipexole of both depressive, and specifically anhedonic, symptoms	Change in QIDS-SR_16_ and SHAPS scores between baseline and week 12 and change in reward sensitivity between baseline and week 2	Baseline, week 2, week 12
To compare the extent to which an increase in reward sensitivity predicts therapeutic response	Change scores in the learning/decision making task at 2 weeks and the change in the QID-SR_16_ at 12 weeks	Week 2, week 12
To explore the extent to which reward sensitivity at baseline predicts therapeutic response	Baseline scores on the learning/decision making task and the change in QIDS-SR_16_ at 12 weeks	Baseline, week 12
To explore the extent to which level of anhedonia at baseline predicts therapeutic response	Baseline scores on SHAPS and change in the QIDS-SR_16_ at 12 weeks	Baseline, week 12
To compare the effect of pramipexole and placebo on the trajectory of symptoms of depression	QIDS-SR_16_ scores collected weekly across 48 weeks of the trial	Weekly for week 1–48
To compare the effect of pramipexole and placebo on response and remission rates, using the QIDS-SR_16_ at twelve weeks	QIDS-SR_16_ response, defined as a reduction of <50% of baseline scores at week 12, remission as a score of <5 at week 12	Baseline, week 12
To compare the impact of pramipexole and placebo on symptoms of anhedonia, anxiety and clinician rated depression	Change scores for the SHAPS, GAD-7 and QIDS-C between baseline and week 12	Baseline, week 12
To compare the impact of pramipexole and placebo on functional outcome over the 48 weeks of treatment	Change scores for the WSAS-screener between baseline and week 48	Baseline, weeks 12, 24, 36 and 48
To determine the impact on quality of life and capability well-being of pramipexole relative to placebo over 48 weeks	Change in the following over 48 weeks: EQ-5D-5L ICECAP-A OxCAP-MH	Baseline, weeks 12, 24, 36 and 48
To examine the health/social care and broader societal costs of patients relative to placebo over 48 weeks	Change in the following over 48 weeks: HEQ	Baseline, weeks 12, 24, 36 and 48

GAD-7, General Anxiety Disorder Scale; HEQ, Health Economics Questionnaire; ICECAP-A, ICEpop capability measure for adults; OxCAP-MH, Oxford CAPabilities questionnaire-Mental Health; QIDS-SR16, quick inventory of depressive symptomatology self-report 16; QUIP-RS, Questionnaire for Impulsive-Compulsive Disorders in Parkinson’s Disease–Rating Scale; SHAPS, Snaith-Hamilton Pleasure scale; TSQM-9, Treatment Satisfaction Questionnaire for Medication Version 9; WSAS, Work and Social Adjustment Scale.

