#### Assignment of intervention

Each participant will be randomised at a ratio of 1:1 to either pramipexole or a matched placebo. A non-deterministic algorithm will be used to produce treatment groups balanced for important prognostic factors by minimising separately on four variables including (1) trial site, (2) age (18–50, vs >50), (3) gender (M/F) and (4) baseline quick inventory of depressive symptomatology self-report 16 (QIDS-SR16) severity (11–15 vs 16–20 vs >20).

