#### QIDS-SR16 and clinician-rated (QIDS-C)

This is a 16-item questionnaire that covers 9 symptoms of depression.^18^ The scale assesses severity of depression and change in depressive symptoms over time. Participants are instructed to score each item according to the description that best describes their experience over the past 7 days. Each of the symptoms is scored on a 4-point scale (0–3) giving a maximum possible score of 27 (not all items contribute to the total). The total score will detect change in depression symptom-severity, while item 12 will additionally act to detect suicidal thoughts. Clinicians will complete QIDS-C during all study visits. Meanwhile, participants will complete QIDS-SR16 on True Colours once per week from screening to Week 12, and then once every 4 weeks up to week 48.

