### Sample size

At week 12, PAX-D considers a three-point difference on QIDS-SR_16_ scores between pramipexole and placebo to be clinically important (with SD of the scores of 5.4 based on those observed in the CEQUEL trial^29^ and produces a standardised effect size of 0.56). The sample size to test differences between groups at 90% power and at a type one error rate of 5% would be 68 per group (136 total), increasing with 20% drop-out to 170 total. To test a similar sized difference in reward sensitivity and to ensure that type one error for both the depression score and the reward sensitivity tests is 0.05 or below, the sample size calculation can be determined using an alpha of 0.025. At an alpha of 0.025 and power of 90%, the required sample size would be 81 per group. Allowing for an estimated 20% lost to follow-up would then increase the sample size to 102 per group (204 total).

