### Statistical methods

The primary outcome (change in QIDS-SR16 between baseline and week 12) will be analysed using a generalised linear mixed model utilising data collected at each weekly time point from randomisation and including the baseline outcome and minimisation factors as fixed effects. The model will include a random intercept for each participant to account for the repeated measures on the same participant and an interaction term for the treatment by time interaction to allow the treatment effect to differ at each time point.

Continuous secondary outcomes will be analysed using generalised linear models. The dichotomous secondary outcomes will be analysed using a logistic mixed effects regression model. These analyses will include a fixed effects randomised group and baseline level of the QIDS-SR_16_, with participants and trial site accounted for as random effects. Minimisation variables will be included as explanatory factors in the models. Mediational analysis will test whether changes in reward sensitivity mediate the effect of pramipexole on depressive symptoms. Health economic data analysis will assess group differences in quality of life, well-being, and work performance using a cost-utility analysis.

The primary and efficacy-based secondary analyses will be performed using an intention-to-treat approach for all randomised participants. Analyses of the mechanistic secondary outcomes and health economic outcomes will be performed in the set of participants who have the data required for the specific analyses (ie, no imputation will be performed for these analyses). Acceptability analyses will be performed on a subgroup of participants and trial clinicians who provide separate consent for aspect of the trial.

The main health economic analysis will include: (1) a detailed patient-level cost analysis of health, social care and other broader societal costs for both the pramipexole and placebo arms of the trial and (2) an incremental within-trial economic evaluation comparing the pramipexole and placebo arms of the trial in terms of their costs and outcomes over the 48-week trial follow-up period.

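### Table 1 defines QIDS-SR16 response with the inequality the wrong way round, so small improvements count as response and large ones, including every remission, do not

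*Protocol article*

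**What the plan says.** Table 1 (Objectives) lists this secondary objective: "To compare the effect of pramipexole and placebo on response and remission rates" at week 12, measured on the QIDS-SR16. The outcome cell of the same row gives both thresholds. Response is "defined as a reduction of <50% of baseline scores at week 12", and the cell continues with "remission as a score of <5 at week 12". The table's caption credits the trial registry as its source.

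The definition of response is not repeated or corrected elsewhere in the article. The description of the QIDS-SR16 gives the scoring, "giving a maximum possible score of 27", but no response rule. Statistical methods says only how such outcomes are modelled: "The dichotomous secondary outcomes will be analysed using a logistic mixed effects regression model".

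Two other places bear on the meaning. Assignment of intervention minimises on baseline QIDS-SR16 in three bands, the lowest being 11–15. The Introduction reports response in an earlier 65-patient trial of pramipexole as 40% vs 27%, where the higher figure is the better one.

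**The concern.** The scale runs from 0 to 27 and improvement is a fall in score, so a response rule should pick out the large falls. The printed rule picks out falls of less than half. It also conflicts with the remission rule beside it, because a participant can be in remission only after a fall that the response rule excludes.

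At stake is the meaning of one published efficacy outcome. If the rule were applied as printed, a higher rate would no longer indicate benefit. If the team instead reports the rule it almost certainly intends, the result will differ from the published definition, and a reader comparing the two will see an unexplained change.

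**Working it through.** **The plan's own figures.** The article computes nothing from the response definition. Its only calculated design figure is the sample size, which rests on a three-point mean difference and an SD of 5.4. With the stated effect size of 0.56, 90% power and a two-sided t-test, I obtain 68 per group at alpha 0.05 and 81 at alpha 0.025, as stated. Allowing for 20% dropout, 68/0.8 = 85 per group (170 total), and 81/0.8 = 101.25, rounded up to 102 (204 total). Response does not enter this calculation.

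**Step 1: the rule applied to single participants.** Reduction = (baseline − week 12)/baseline. For a baseline of 20:
- week 12 score 18: reduction 2/20 = 10%, which is below 50%, so a responder as printed;
- week 12 score 8: reduction 12/20 = 60%, so not a responder as printed.

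**Step 2: response against remission.** The lowest baseline in the minimisation bands is 11, and the highest remission score is 4. The smallest possible fall for a remitter is (11 − 4)/11 = 63.6%. Higher baselines give larger falls; at 16 the minimum is (16 − 4)/16 = 75%. No remitter can satisfy the printed response rule.

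**Step 3: all possible scores.** Baselines 11–27 (17 values) and week 12 scores 0–27 (28 values) give 17 × 28 = 476 pairs.

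| Change from baseline | Pairs |
|---|---|
| Reduction of at least 50% | 174 |
| Some reduction, but below 50% | 149 |
| No change or worse | 153 |

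If no change and worsening count as a reduction below 50%, the printed rule covers 149 + 153 = 302 pairs, and 302 + 174 = 476, so it is the exact complement of a reduction of at least 50%. If they do not count, the printed rule covers 149 pairs and is not a complement.

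**Step 4: effect on the arm comparison if the rules are complements.** Take 40% and 27% as assumed true response rates. They are results of the earlier trial, not planning values for PAX-D.
- At least 50%: odds ratio = (0.40/0.60)/(0.27/0.73) = 1.80.
- As printed: 60% vs 73%, odds ratio = (0.60/0.40)/(0.73/0.27) = 0.55 = 1/1.80.

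The log odds ratio changes sign and keeps its size.

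**Step 5: effect if only actual falls count.** Assume week 12 scores are normal with SD 5.4, a common baseline *b*, a placebo mean improvement of 2, 4 or 6 points, and 3 points more on pramipexole. The printed rule's rate is then Φ((*b* − mean)/5.4) − Φ((*b*/2 − mean)/5.4).
- *b* = 16, placebo improvement 4: pramipexole 0.903 − 0.427 = 47.6%; placebo 0.771 − 0.229 = 54.1% (differences taken before rounding). The drug looks worse.
- *b* = 20, placebo improvement 2: pramipexole 0.823 − 0.177 = 64.6%; placebo 0.644 − 0.069 = 57.5%. The drug looks better.

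Over baselines 13, 16 and 20 crossed with the three placebo improvements, the narrower reading favours placebo in 7 of 9 settings and pramipexole in 2. Under the complement reading the direction inverts in all 9.

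**The case against.** The strongest reply is that this is an evident slip that no analyst would code. The same row pairs response with remission, the Introduction treats more response as better, and a derivation under which no remitter responds would be noticed at once. The article is also a condensed account; it points to a full ethically approved protocol, and an SAP may exist. Much of this stands. It limits the consequence, but it does not make the printed rule correct. The article did not leave the definition to another document; it stated one.

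Three stronger readings are tempting, and the document does not support them:
- **That unchanged and worsened participants are certainly responders.** Someone who has not improved has arguably had no reduction at all. The text does not settle this, and the exact inversion depends on it, as steps 3 to 5 show.
- **That 60% vs 73%, or 0.55, is the expected distortion in this trial.** The 40% and 27% come from a different study, whose response definition the article does not give.
- **That the analysis will be run in reverse, or that the code is wrong.** Nothing shown says so. Even under the complement reading the change is a relabelling: the absolute difference between arms is the same 13 percentage points (40 − 27 = 13 and 73 − 60 = 13).

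One further point in reply also stands. The phrase may be a slip for a score falling to less than half of baseline, and not for a fall of at least half. The two differ only at exactly 50%, which an integer score can reach at the eight even baselines from 12 to 26, so in 8 of the 476 pairs.

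**Conclusion.** The definition is wrong as printed. Whichever way zero change is handled, it admits a 10% improver, rejects a 60% improver and excludes every remitter. The last point assumes only that baseline scores are at least 11, as the minimisation bands imply.

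The inversion of the arm comparison is conditional: it is exact if no change and worsening count as reductions below 50%, and otherwise its direction depends on the score distribution. The odds ratios of 1.80 and 0.55 are illustrative and unadjusted.

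The error concerns one secondary outcome. The primary outcome is continuous change in QIDS-SR16 and does not use the rule; nor does the sample size. It should be corrected, but it does not threaten the trial's main conclusion.

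**What to change.** Restate the Table 1 entry as: response is a reduction of at least 50% from the baseline QIDS-SR16 score at week 12, with exactly 50% counting as response. The investigators should confirm that this boundary is the one they intend.

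Then check that the registry entry from which the table is taken, the full protocol, the SAP and the derivation code all carry the same definition, and correct any that do not. A simple test in the code is that every remitter with a baseline of 11 or more must also be a responder.

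The cost is a one-line correction and a short cross-check, best dated before unblinding. It needs no new data and does not change the sample size or the primary analysis.
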